## Abstract

**Background:**

People with low literacy and low health literacy have poorer health outcomes. Literacy and health literacy are distinct but overlapping constructs that impact wellbeing. Interventions that target both could improve health outcomes.

**Methods/design:**

This is a cluster randomised controlled trial with a qualitative component. Participants are 300 adults enrolled in basic language, literacy and numeracy programs at adult education colleges across New South Wales, Australia. Each adult education institute (regional administrative centre) contributes (at least) two classes matched for student demographics, which may be at the same or different campuses. Classes (clusters) are randomly allocated to receive either the health literacy intervention (an 18-week program with health knowledge and skills embedded in language, literacy, and numeracy training (LLN)), or the standard Language Literacy and Numeracy (LLN) program (usual LLN classes, specifically excluding health content).

The primary outcome is functional health literacy skills – knowing how to use a thermometer, and read and interpret food and medicine labels. The secondary outcomes are self-reported confidence, more advanced health literacy skills; shared decision making skills, patient activation, health knowledge and self-reported health behaviour. Data is collected at baseline, and immediately and 6 months post intervention. A sample of participating teachers, students, and community health workers will be interviewed in-depth about their experiences with the program to better understand implementation issues and to strengthen the potential for scaling up the program.

**Discussion:**

Outcomes will provide evidence regarding real-world implementation of a health literacy training program with health worker involvement in an Australian adult education setting. The evaluation trial will provide insight into translating and scaling up health literacy education for vulnerable populations with low literacy.

**Trial registration:**

Australian New Zealand Clinical Trials Registry ACTRN12616000213448.

**Electronic supplementary material:**

The online version of this article (doi:10.1186/s12889-016-3034-9) contains supplementary material, which is available to authorized users.

## Background

### Low literacy and health literacy

Health literacy is commonly defined as the *capacity to acquire, understand and use information in ways which promote and maintain good health* [1, 2]. As with general literacy, health literacy skills can be described and measured at different levels: “functional” (the health skills required to function in everyday situations), “communicative/interactive” (more advanced skills to extract information, discriminate between different sources of information and derive meaning) and “critical” (the ability to critically analyse information) [3, 4]. Health literacy involves the capacity to *use* health information, not simply to obtain it [3].

To the extent that health literacy involves engaging with written information, it is strongly influenced by language, literacy and numeracy (LLN); hence some commonly used measures of health literacy (e.g. REALM [5], TOFHLA [6]) measure recognition and use of health vocabulary. Individuals with limited literacy skills are less likely to engage in preventative healthcare, are more likely to develop chronic illnesses [7] and, once developed, experience greater difficulties managing those illnesses and often die earlier [8]. In Australia, up to 60 % of adults lack basic health literacy skills to understand health-related materials, such as instructions on a medicine label [9]. Estimates of low health literacy in Europe (47 %) [10] and the US (36 %) [11] are similarly high. Building health literacy is a priority in Australia and internationally [10, 12–14].

Closely aligned with emerging interest in population heath literacy has been a growing recognition of the value of Shared Decision Making in health care. Shared Decision Making occurs when patients and health professionals work together to jointly make decisions about a patient’s health [15, 16]. It is a cornerstone of high quality healthcare and now endorsed by major health organisations internationally [13, 17, 18]. Research shows that patients who share health decisions have higher health knowledge, more accurate risk perceptions, reduced difficulty with decision-making [19, 20], and in some circumstances show improved clinical outcomes [21–23]. Shared Decision Making and involvement in health care generally may be viewed within Nutbeam’s conceptual framework as “communicative” and “critical” health literacy. Yet there has been relatively little effort to support Shared Decision Making for adults with low general literacy and it has not been incorporated into health literacy programs to date [24]. There is a need to both develop and test health literacy interventions that support Shared Decision Making for adults with lower levels of general literacy.

### Health literacy interventions

Partnerships between health and education agencies offer promise in building health literacy in the population [25], especially if they collaborate to access hard-to-reach groups and develop strategies to improve both health literacy, and general language, literacy, and numeracy (LLN) skills [26, 27]. The field of adult literacy has been cautious about integrating health content into adult education programs due to concerns that teachers may lack the expertise and confidence to deliver topics about health [28]. This is changing, although rigorous evaluations are lacking.

In the US, the Health Literacy Study Circles is a program providing teachers tools to develop health-related units, lessons and action plans [29]. The program as part of a broader intervention has been reported to increase students’ health-related knowledge and self-efficacy [30]. Three ‘health literacy’ style programs have been run in adult education settings and evaluated in randomised trials in the US [31–33]. Although published work has indicated some degree of success of these programs [32], only one was published in a peer reviewed journal [33] making it difficult to ascertain how effective these programs have been. The one published study, a trial of a community-based health literacy/English as a Second Language program was targeted at Hispanics in the United States. It showed promising increases in health-related verbal fluency (using the TOFHLA) in the health literacy arm [33] immediately post intervention but there was no further follow up and measures focused on a functional health literacy only.

A UK based program that embedded health content into adult basic education was the *Skilled for Health* program [34]. It found that health content helped to engage and retain socially disadvantaged adult learners and participants reported improved understanding about health and healthier behaviours (diet, exercise and smoking). However, improvements in specific health literacy skills were not directly assessed and health literacy and health behaviour outcomes were measured by self-report. Additionally the study did not use a randomised design and lacked a control group for rigorous comparison [34].

### The Australian health literacy program

We aim to evaluate the efficacy of an intervention similar to Skilled for Health, adapted for an Australian context using a randomised trial design, with outcomes assessed immediately post intervention and at 6 months to determine whether any health literacy gains are retained.

A novel addition to the program in this study is the development and inclusion of a Shared Decision Making component (see [35]). This seeks to teach students about the concept of Shared Decision Making (i.e. teaching them that there are often different test and treatment options, that they have a choice between options, and that they have the right to ask questions); provide education about probability and risk, (i.e. how to understand the outcomes and likelihood of different options); and develop self-efficacy to express preferences and be actively involved in health decisions. Specifically, we introduced the AskShareKnow questions [36] to students (What are my options? What are the possible benefits and harms of those options? How likely are each of those benefits and harms to happen to me?) as a generic Shared Decision Making tool to help achieve these aims. The AskShareKnow questions have been shown to increase the amount and quality of information about treatment options provided by family physicians and increase Shared Decision Making behaviours in consultations [36], and the demonstration of these questions via a short video clip in a clinic waiting room was found to be a feasible approach to increase question asking in health care consultations [37].

The population of adults attending basic LLN classes in Australia comprises two distinct groups: native English speakers (mostly Australian-born) who may have experienced a range of learning disabilities, did not complete school, or are retraining as a condition of their unemployment benefits; and (migrants) from culturally and linguistically diverse backgrounds (CALD) who may fit any or none of the above conditions. Some of these migrants are highly-educated, but have poor (oral and/or written) English skills; others may have never attended school. The challenge is to develop a program flexible enough to cater to the different needs of these populations and deliver measureable differences in health literacy outcomes.

### Study objectives

This is a cluster randomised controlled trial that aims to evaluate a best practice model to:Deliver improvements in health literacy, confidence in health skills, Shared Decision Making, and knowledge about health and healthy behaviour, through a health literacy education program.Demonstrate improved engagement in learning (through higher attendance at classes) and greater enrolment in further adult education classes.Assess feasibility for delivery in a variety of locations (metropolitan, regional, and remote).

The health literacy program will be compared to a standard adult language, literacy and numeracy (LLN) program which would be expected to achieve some improvements which extend to health literacy outcomes also. Therefore this trial will examine the added benefit the health literacy program brings to health literacy related outcomes.

## Methods

### Study design

This study is a matched cluster randomised controlled trial (Fig. 1), in which a class represents a cluster. Each participating institute will be required to provide (at least) one matched pair of classes, in which a pair comprises one intervention and one standard LLN class. The two classes within each pair will be a priori matched for typical student demographics (e.g. day or evening students; metropolitan or regional; predominance of native English or NESB students) and enrolled in the same course code.

**Fig. 1 Fig1:**
[figure not shown]
Flowchart of study activities

Intervention and standard LLN classes will have the same TAFE-specified units of competency to cover. Students in the health literacy (“intervention”) classes will learn literacy and numeracy skills with content focused on health topics; the standard LLN classes will cover the same literacy and numeracy skills, in contexts other than health. These “standard LLN” classes control for both expected literacy gains as well as any research participation effects [38].

### Ethics and dissemination

The study has ethical approval from the University of Sydney Human Research Ethics Committee and 10 NSW Institutes of TAFE. Results will be published in peer reviewed journals, and reported to partner organisations. Written informed consent will be obtained from all participants.

### Recruitment

Students and teachers will be recruited from TAFE institutes in NSW, Australia. There are 10 Institutes of TAFE in NSW – each one will be invited to join the study for a full (18-week) semester, and to contribute at least one matched pair of classes delivering the same TAFE course (in the same or different location).

All students enrolled in each participating class will be invited to participate in the study during the first class. To assist recruitment, the researchers (KM, SM, DM) created a video introducing themselves and explaining the purpose of the study.

Participating classes will be basic LLN courses corresponding to Level 2 (basic/beginner) of the 5-level Australian Core Skills Framework (ACSF). The ACSF describes performance on the 5 skills of learning, reading, writing, oral communication, and numeracy, and is assessed by TAFE teachers at student enrolment. Each TAFE course has a designated code, and specifies LLN learning outcomes that students must achieve. For relevant course codes, a “mapping” document produced by a TAFE coordinator indicates which units of the health literacy program cover each LLN competency.

### Randomisation

At enrolment, students will be allocated to classes following normal TAFE procedures. Classes will be randomised centrally into “intervention” or “standard LLN” groups by the University of Sydney team. At campuses holding only one class participating in the study, all enrolling students will be allocated to that class. At larger metropolitan campuses with more than one participating class, students will be randomised into classes on enrolment day, by selecting an “odd” or “even” paper ticket. Matched classes at the same location will be held on different days to minimise risk of contamination between intervention and standard groups.

### Participants and setting

Participants will be recruited following standard TAFE processes for enrolling students. Participating TAFE teachers will invite 300 adults assessed at ACSF level 2, seeking basic education at TAFE in NSW to join the study. As part of standard procedures, students’ literacy and numeracy levels are assessed by TAFE teachers on enrolment day.

### Participating sites

We will recruit classes from TAFE Institutes in metropolitan and regional centres across NSW, Australia, including multiple Sydney districts, and Illawarra, Hunter, New England, and Southern NSW.

### Inclusion criteria

Eligible classes will be learning basic language, literacy and numeracy at ACSF level 2 (in one of 4 eligible course codes). Intervention and standard LLN classes will be matched on typical demographic characteristics including age, sex, English proficiency, literacy skills, course code, and region. Students will be 16 years and older. Consent from a parent or guardian must be obtained for students under 18 years.

### Intervention: the health literacy program

Australian adult education and public health experts adapted the UK *Skilled for Health* program to an Australian context. The revised program embeds key LLN skills development at the Australian Core Skills Framework level 2 into materials containing health-related topics focused on public health priorities (as identified by NSW Health) using Functional Context Education (FCE) methods [39]. In this approach students learn specified LLN skills through engaging with health material guided by their teacher [40]. We added a Shared Decision-Making program centred around the AskShareKnow questions (as described in [35]) that teaches participants about participating in decision making about their health, using recommended questions to elicit information from healthcare professionals, and discussing how to understand their responses.

The program consists of two teaching manuals:“Being Healthy”, which covers health skills such as using a thermometer, understanding prescriptions, communicating with health professionals, and Shared Decision-Making; and“Staying Healthy”, which focuses on diet and exercise (healthy lifestyle).

The 16 Being Healthy and 14 Staying Healthy topics are listed in Table 1. Teachers will be given a suggested delivery plan, with advice that they may diverge from this, according to the interests and capabilities of their students. The main requirement for delivery is that classes cover all 10 “core” topics considered central to the health literacy learning objectives and linked to the quantitative assessments. For the remainder of lessons students and teachers can select topics of most interest and relevance to the class.

**Table 1 Tab1:** Course content

Being healthy Teacher manual 1	Staying healthy Teacher manual 2
1.1 Taking temperature^a^	2.1 Getting involved
1.2 Checking medicine labels^a^	2.2 Food groups
1.3 Prescriptions	2.3 Food labels^a^
1.4 Dosage and timing	2.4 Nutritional information^a^
1.5 Health workers	2.5 Food temperature safety
1.6 Telling your doctor what is wrong^a^	2.6 Food date safety
1.7 Talking to your doctor^a^	2.7 What is a serve?^a^
1.8 Answering your doctor’s questions^a^	2.8 Budgeting
1.9 Immunisation and health screening	2.9 Understanding a diet
1.10 Asking questions^a^	2.10 Drinking enough fluids
1.11 Shared decision-making^a^	2.11 Heart Rate and Pulse
1.12 Completing medical forms	2.12 Being Active
1.13 Emergency services	2.13 Watch First Aid demonstrations
1.14 Advice from pharmacist	2.14 Follow written instructions
1.15 Saving lives	2.15 Talking on the telephone
1.16 Follow emergency instructions	Revision/Goal setting

^a^Core topic

Development and piloting of the teacher manuals is described elsewhere [41]. Following the pilot, the program was modified in response to participant feedback; and sent to Australian health experts (including partner organisations NSW Health, NPS Medicine Wise, NSW Clinical Excellence Commission) for review. The final manuals can be obtained from the corresponding author.

### LLN (standard LLN) program

Standard LLN students will complete the “standard” TAFE content for the units of study. This includes learning computer skills, employment skills, and other non-health related activities and is designed to develop core skills and confidence in language, and improve functional English language, literacy and numeracy skills.

### Sample size

The primary outcome for sample size calculation is the functional health literacy score used in our pilot study ([41]). We estimate that 86 students are required per group to detect a difference in the mean total score between the intervention and standard LLN groups of 0.5 standard deviation (SD) with 90 % power at the two-sided 5 % significance level. An established systematic review indicates that a half-standard deviation is the ‘threshold of discrimination’, or the minimally important difference, for changes to psychosocial outcomes in chronic disease assessment [42]. To allow for clustering within a class and using an intra-cluster correlation coefficient of 0.05 and an average class size of 10, the required sample size is 125 students. Allowing for 15 % loss to follow-up, we aim to recruit 150 participants in each arm (*n* = 300 in total; 15 pairs of classes of approximately 10 students per class). This sample size will also be sufficient to detect a difference in retention of at least 20 % between the intervention and standard LLN group, with 80 % power. Due to the unpredictability of TAFE enrolments, unequal cluster sizes are assumed.

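### The plan says class sizes are assumed unequal, but 125 per arm is the equal-size answer with student-level degrees of freedom, so required size is understated and power modestly overstated

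*Protocol article*

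**What the plan says.** The Sample size section of the protocol article starts from a difference of 0.5 SD "with 90 % power at the two-sided 5 % significance level" and concludes that "86 students are required per group". It then allows for clustering "using an intra-cluster correlation coefficient of 0.05 and an average class size of 10", and reports that "the required sample size is 125 students". The words per arm are missing there, but they follow from the 86 per group and from the recruitment target of 150 per arm. Attrition of 15% raises the target to 150 per arm, which the section describes as 15 pairs of classes with about 10 students in each. The paragraph ends: "Due to the unpredictability of TAFE enrolments, unequal cluster sizes are assumed". No CV or range of class sizes is given. Under Study design the class is the cluster and classes are matched in pairs. Under Statistical analysis the primary comparison is a regression that accounts for clustering, by a method not named.

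**The concern.** The closing sentence and the calculation before it do not fit together. A reader will take it that variation in class size is already inside the 125 and the 90%. If the 125 comes from a formula for equal classes, no such allowance is there, and any real variation raises the number needed. The starting figure of 86 also treats students as the units that supply the degrees of freedom, whereas the comparison rests on about 15 classes per arm. Both omissions work in the same direction: they make the required size look smaller and the power look higher than the stated assumptions support. At stake is whether the trial has the power it claims for its primary outcome.

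**Working it through.** **Inputs from the Sample size section.** Difference 0.5 SD; 90% power; two-sided 5%; ICC 0.05; average class size 10; loss 15%; 15 classes per arm. **Assumed here:** CV of class size, shown from 0 to 0.6.

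**1. Reproduce the plan's figures.**
- Two-sample t-test for 0.5 SD: 85.03, rounded up to 86 per group.
- Equal-size design effect: 1 + (10 − 1) × 0.05 = 1.45.
- 86 × 1.45 = 124.7, rounded up to 125.
- 125 / 0.85 = 147.1, so 148, which the plan rounds to 150.

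All the figures reproduce, and the 125 uses CV = 0.

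**2. Required size with unequal classes averaging 10.** The design effect becomes DE = 1 + [(1 + CV²) × m − 1] × 0.05, with m = 10:
- CV 0.3: DE 1.495; 86 × 1.495 = 128.6, so 129
- CV 0.4: DE 1.530; 86 × 1.530 = 131.6, so 132
- CV 0.5: DE 1.575; 86 × 1.575 = 135.5, so 136
- CV 0.6: DE 1.630; 86 × 1.630 = 140.2, so 141

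**3. Power at the stated 125 per arm.** The effective number per arm is n_eff = 125 / DE. The noncentrality is 0.5 × √(n_eff / 2). With classes of 10 there are 12.5 classes per arm, so the class-level degrees of freedom are 2 × 12.5 − 2 = 23.

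| CV | Normal approximation | t on 23 df |
|---|---|---|
| 0 | 90.7% | 88.2% |
| 0.4 | 89.2% | 86.4% |
| 0.6 | 87.2% | 84% |

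On class-level degrees of freedom, 125 falls short of 90% even with equal classes.

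**4. Power of the trial as recruited.** There are 150 / 15 = 10 recruited per class. After 15% loss, 8.5 per class are analysed, or 15 × 8.5 = 127.5 per arm. The same formulas apply with m = 8.5 and 2 × 15 − 2 = 28 df. The last column gives 14 df (15 pairs − 1) with no gain from matching.

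| CV | DE | n_eff | Normal | t, 28 df | t, 14 df |
|---|---|---|---|---|---|
| 0 | 1.375 | 92.7 | 0.926 | 0.908 | 0.886 |
| 0.3 | 1.413 | 90.2 | 0.919 | 0.900 | 0.877 |
| 0.4 | 1.443 | 88.4 | 0.914 | 0.894 | 0.870 |
| 0.5 | 1.481 | 86.1 | 0.907 | 0.886 | 0.862 |
| 0.6 | 1.528 | 83.4 | 0.898 | 0.876 | 0.851 |

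**5. Design effect alone, at the analysed class size.** The need is 86 × DE with m = 8.5: 121.5, 124.1, 127.4 and 131.4 at CV 0.3, 0.4, 0.5 and 0.6, against 127.5 expected. The recruited number therefore covers inequality up to a CV of about 0.5 if the number of classes is ignored. At CV 0.6 it is about 4 students per arm short.

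**The case against.** The strongest defence is that nothing has been miscalculated. Every figure reproduces, and the closing sentence can be read as describing expected conditions and not as claiming an allowance within the 125. Small-sample degrees of freedom are often left to an analysis plan. This stands in part: the fault is a mismatch between a stated assumption and the formula used, not a slip in multiplication. It does not remove the point, because the article prints the inputs, the result and the assumption together, and the result does not reflect the assumption.

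A reader might go further in three ways that the document does not support.

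- **That more students must be recruited.** Dividing 132 to 141 by 0.85 gives 156 to 166 per arm, which seems to exceed 150. That treats 10 as the class size after loss. The plan's 150 in 15 classes makes 10 the recruited size, so the analysed size is 8.5 and most of the apparent shortfall disappears.
- **That power falls to 85–87%.** At CV 0.4 to 0.6 this requires a pair-level test on 14 df with nothing gained from matching. The Statistical analysis section does not specify such a test, and matching may well bring some gain, though no figure is given.
- **That baseline adjustment makes up the loss.** The Statistical analysis section places baseline adjustment among the secondary analyses, and the Immediate post intervention outcomes section shows that the food-label component has no baseline measurement. No correlation is given from which a gain could be worked out.

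**Conclusion.** The point holds in a limited form. The 125 per arm is the equal-size answer with student-level degrees of freedom, which contradicts the stated assumption of unequal classes. At 125 analysed per arm, the required size is understated by about 7 to 16 students (132 to 141) for an assumed CV of 0.4 to 0.6, and power on 23 df is 86% to 84%, not 90%. For the trial as recruited the overstatement is small. On 28 df, power is at or above 90% up to a CV of about 0.3, and 89.4% to 87.6% at CV 0.4 to 0.6, a loss of roughly one to two and a half points. These results take the plan's ICC of 0.05, its 15% loss and its 15 classes per arm as given. The exact size depends on a CV that the document does not state. The design remains sound; the stated figures need correcting.

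**What to change.** Keep 15 pairs and 300 students. In the Sample size section, state the assumed CV of class size and its basis. Replace the design effect by 1 + [(1 + CV²) × m − 1] × 0.05 with m the analysed class size (8.5 after 15% loss), and use class-level degrees of freedom. Restate the power for 0.5 SD: about 88–90% on 28 df for CV 0.3 to 0.6. Add per arm to the 125.

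If no CV can be justified, say instead that 125 assumes equal class sizes and remove the sentence on inequality. In either case, do not write that a baseline-adjusted primary model restores the power.

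The cost is a few reworded sentences and a slightly less favourable stated power. Recruitment, design and analysis do not change.
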